## Abstract

Dementia caregiving, besides encompassing various challenges in tandem to the diagnosis of the care recipient, is associated with decreased psychological well-being and mental health. Accordingly, caregivers’ wellbeing has an impact on the quality of care they provide and on the relationship quality with the person in their care. The aim of the present study is to examine the effectiveness of a mindfulness-based intervention on relational and psychological wellbeing, tailored to the needs of dementia caregivers. This clinical trial (NCT04977245) will apply a randomized controlled mixed method design. Caregivers will be randomly allocated to either the mindfulness intervention or the active control group. The intervention arm is based on experiential learning and is targeted to promote caregivers’ well-being and empowerment. Assessments will include, standardized self-report questionnaires, task performance measures, and qualitative measures. All assessments will be held at three time points (baseline; t0, 0 months, post-intervention; t1, 2 months, and after maintenance; t2, 3 months) focused on three core domains (1. relational well-being, 2. psychological well-being, and 3. dementia patient’s lifestyle/activities). The primary outcome will be relational well-being, and data will be analyzed using linear mixed modelling.

## Introduction

While caring for someone with dementia can have many positive personal and relational outcomes, it can also be a very challenging task encompassing various practical and psychological demands (Quinn et al., 2009; Sörensen and Conwell, 2011; Fontaine et al., 2016; Li et al., 2016). Common adverse experiences for caregivers include over-engagement in caregiving tasks, significantly limited discretionary time, reduced access to socioemotional support, and complications related to finances and employment (Connell et al., 2001; Bertrand et al., 2006). In parallel with those challenges, caregivers often experience difficulties with mental health and psychological and relational well-being (Rabins et al., 1982; Bledin et al., 1990; Pinquart and Sörensen, 2003, 2006), which can manifest as burden, depressive symptoms, negative affect, social isolation, as well as decreased relationship quality between themselves and their care recipient (Wagner et al., 1997; Quinn et al., 2009). Caregiving demands often sustain over time and can engender significantly maladaptive psychological processes. For instance, rumination can prolong intensified feelings of negativity toward one’s role as a caregiver (Aldao et al., 2010; Guendelman et al., 2017), while criticism and emotional over-involvement with the care recipient reflect poor relationship quality and predict caregivers’ strain levels (Morris et al., 1988; Fearon et al., 1998). Caregivers who associate the quality of the relationship with their care recipient with intensified negative emotions (e.g., guilt, anger, grief) are more likely to exhibit poor coping skills (Lea Steadman et al., 2007; Shaffer et al., 2007; Cooper et al., 2010a,b; Manteau-Rao and Barrows, 2016).

Caregivers of dementia patients face additional specialized challenges that differ in tandem with the particular diagnosis and behaviors exhibited by the care recipient (Yeager et al., 2010; Leggett et al., 2011; Wong et al., 2012; George et al., 2020). Hence, a need for effective interventions to assist dementia caregiving challenges naturally emerges. While Alzheimer’s disease (AD) patients exhibit memory and cognitive dysfunction, patients with frontotemporal dementia (FTD) primarily exhibit emotional bluntness, apathy, and behavioral disinhibition (e.g., outbursts, inappropriate, or risky behaviors; Pinquart and Sörensen, 2004, 2007). Accordingly, compared to AD caregivers, FTD caregivers, and particularly those whose patient is diagnosed with the behavioral variant of FTD (bvFTD), experience significantly higher distress and strain levels, more depressive symptoms, lower perceived control, greater burden, and poorer satisfaction with the care recipient and themselves (de Vugt et al., 2006; Riedijk et al., 2006; Boutoleau-Bretonnière et al., 2008; Ascher et al., 2010). Other neurodegenerative conditions in which early behavioral changes occur, like Huntington’s disease (HD), create important challenges for family caregivers, including compromised quality of life and difficulties in communication (Hartelius, 2010; Aubeeluck et al., 2011).

Past research examining psychosocial interventions for dementia caregivers (e.g., support groups, psychoeducation, counseling) reveals inconsistent evidence for their effectiveness in decreasing burden and depression (Cooke et al., 2001; Dam et al., 2016; Collins and Kishita, 2018). However, early evidence suggests that mindfulness-based stress reduction (MBSR) programs may be effective for dementia caregivers. Mindfulness training *via* the MBSR program cultivates skills of non-reactivity, acceptance, and awareness, which may work against reactive coping mechanisms in caregivers, ultimately enhancing attributes connected to psychological well-being (Kabat-Zinn, 1992; Killingsworth and Gilbert, 2010; Lindsay and Creswell, 2017). Mindfulness may additionally impact downstream emotion regulation processes that introduce flexibility in generating cognitive appraisals, thereby facilitating savoring of positive experiences. This improved regulation is proposed to culminate in a deepened capacity for meaning-making and greater life fulfillment (Garland et al., 2009). Mindfulness is, additionally, associated with improving compassion and kindness toward oneself and others (Neff, 2003). Skills of compassion and kindness seem to accordingly protect from self-criticism and rumination by improving emotional connection to others (*via* increasing empathy and reducing emotional reactivity; Van Doesum et al., 2013; Lin et al., 2016; Campos et al., 2019).

Studies investigating the potential benefits of mindfulness-based interventions to dementia caregivers highlight the importance of two fundamental pillars that mindfulness aims to cultivate: acceptance and a non-judgmental awareness (Spira et al., 2007; Jaffray et al., 2015; Krishnan et al., 2017). Adopting mindfulness skills has been shown to help caregivers acknowledge difficulties in their caregiving role and cultivate a focus on the present moment, rather than on past or future events. Mindfulness-based interventions can also reduce caregiver burden and distress, ultimately cultivating skillful coping strategies. For instance, caregivers of patients with HD, after undergoing mindfulness-based cognitive therapy, reported reduced psychological distress coupled with improved emotion regulation. Consequently, ruminative and worrying thoughts were reduced, highlighting that focusing on the present moment reduces distress and allows savoring of the present (Eccles et al., 2021).

Despite some studies showing evidence that mindfulness and compassion impact social cognition (e.g., empathy), very little is known about the association between mindfulness and relationship quality in dementia patient-caregiver dyads. It remains unclear whether mindfulness can improve relationship quality between caregivers and demented patients, making them more closely connected, empathic, or positive. However, by broadening caregivers’ perspective and helping them regulate their automatic reactions, mindfulness may support caregivers’ ability to respond more effectively to challenging communications in the context of dementia care (Garland et al., 2009; Lindsay and Creswell, 2017).

To further investigate those questions, we designed a randomized controlled trial to study the effectiveness of the novel mindfulness-based intervention we specifically tailored to the needs of dementia caregivers. We hypothesize that the mindfulness intervention, compared to the active control group, will lead to (A) an improved relational well-being (primary outcome), (B) a greater psychological well-being (secondary outcome), and (C) a positive impact on dementia patients’ activities (tertiary outcome).

## Methods and analysis

### Design

We will conduct a randomized, controlled trial in which participants will be randomly allocated to either the intervention group (an 8-week mindfulness course tailored to dementia caregivers’ needs), or to the active control arm mimicking the intervention group’s structure (an online self-guided 8-week emotion regulation program). Participants will undergo mixed-method assessments at three time points: baseline (T0, at month 0), post-intervention (T1, at month 2), and after the maintenance phase (T2, at month 5). The study is designed and powered to gather preliminary information on the intervention at the level of an exploratory pilot study. The intervention is designed to be appropriate for caregivers of patients with all categories of dementia, including those with primary deficits in memory, behavior, language, other cognition, or motor functioning.

### Setting

The study will be run virtually in the United States at the University of California, San Francisco (UCSF). Dementia caregivers will be recruited through a dementia clinic research registry, and by local advertisements and recruitment talks; caregivers do not need to be local to the San Francisco Bay Area to participate. The mindfulness-based intervention group will follow a live-online and interactive program (*via* Zoom). It will be led by two certified MBSR teachers who completed their advanced teacher training at the Centre for Mindfulness Studies (Toronto, Canada). The active control group will follow an online, self-guided emotion regulation program and will participate in support group discussions with other caregivers, held twice during the 8 weeks and moderated by a clinical psychologist (*via* Zoom).

### Participants

Eligible participants need to be (1) 18 years of age or older, (2) caregiving for a person with dementia in their personal life with regular (at minimum weekly) contact with them, (3) English speaking, (4) literate (i.e., being able to read course material), (5) able to attend weekly online classes *via* Zoom, and (6) willing to be randomized and participate in one of two interventions. Participants will be excluded from the study on the basis of (1) regularly practicing mindfulness meditation, mindful yoga, similar mindfulness activities or having received prior formal training in MBSR in the past 5 years, (2) currently experiencing active or unresolved trauma without professional psychological assistance, (3) diagnosis of psychosis (e.g., schizophrenia, schizoaffective disorder, or bipolar disorder according to the DSM-IV) or undergoing treatment for substance abuse, (4) acute suicide plans as measured by the Patient Safety Screener (PSS-3), (5) clinical diagnosis of dementia, and (6) uncorrected vision or hearing severe enough to limit their participation in the study.

### Sample size calculation

Because this is a novel study and there are no published effect sizes for the impact of this mindfulness-based intervention on our various outcomes, this study will establish preliminary effect sizes for all measures. Due to the highly interpersonal nature of the mindfulness intervention, enrolling more than 20 participants per arm was impractical; however, considering expected attrition, this sample size will only be powered to detect large between-group effect sizes (i.e., 80% power to detect *r* > =0.70; 25% power to detect *r* > = 0.50).

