### Recruitment, consent, and allocation to interventions

Participants will be recruited by local advertisements and recruitment talks in the San Francisco Bay Area, online dementia caregiving groups, and by accessing an established research registry database. Recruitment is planned to continue until 40 eligible participants are enrolled (20 per intervention arm), and the approximate recruitment period is 2 months. Participants will not receive financial compensation for taking part in the study, and there will be no inducements for completing interventions. Participants deemed suitable for recruitment, will be contacted *via* email or phone with an opportunity to participate in additional eligibility screening, and to complete an online screening questionnaire to confirm eligibility. A follow-up email will include a review of study details (e.g., start date, expectations).

All screening and recruitment conversations will be completed by research personnel trained in the ethical conduct of human subjects’ research. Informed written consent will be obtained *via* interview with a trained examiner (*via* Zoom), during which the study will be clearly explained in detail, and caregivers will be able to ask questions prior to enrollment. Caregivers will also be informed that they can drop out of the study at any time. After this conversation, those agreeing to participate will be asked to formally consent to study participation. Due to current pandemic restrictions, DocuSign will be used to obtain participants’ consent signatures electronically. The amount of time expected for this consenting process is 20 min.

Next, for the baseline assessment part of the study (T0, 0 months), enrolled participants will be scheduled to participate in a 10-min semi-structured online interview *via* Zoom (see Supplementary material) and will complete a set of online surveys and performance tasks *via* Qualtrics. Those evaluations are designed to minimize possible subject fatigue, stress, and boredom. Breaks from testing will be allowed, and testing sessions may also be broken into multiple sessions. After all participants have completed enrollment and baseline assessment, they will be randomized to one of the two study arms and will then be informed *via* email of the group to which they have been assigned (see Figure 1; Table 1).

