**Figure 1 fig1:**
[figure not shown]
Planned flow of participants.

**Table 1 tab1:** Schedule of enrolment, interventions, and assessments.

Timepoint	Study period				
	Enrolment	Randomization	Intervention		Close-out
	*t_−1_*	*t_0_*	*t_1_*	*t_2_*	*t_x_*
Enrolment					
Eligibility screen	X				
Informed consent	X				
Allocation		X			
Interventions					
*MBSR adapted program*					
*GARDEN*					
Assessments					
*Primary outcome*		X	X	X	
*Secondary outcome*		X	X	X	
*Tertiary outcome*		X	X	X	

Randomization with 1:1 allocation ratio to one of the two arms will be conducted by a study investigator with no participant contact. Participants will be randomly allocated *via* a computerized random number sequence, generated *via* the R software (Team, 2014). Allocation will remain concealed from the study staff and participants during screening until randomization is completed.

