### Data analysis plan

The study will use mixed methods, integrating quantitative and qualitative strategies, making no assumptions about linear relationships between quantitative and qualitative data/findings (DePoy and Gitlin, 1994). These two strategies will be employed as different ways of exploring and understanding the theme in question, i.e., mindfulness and caregiver wellbeing.

Regarding quantitative measures we will first identify factors that are confounders between the two intervention groups, which may include socio-demographics, relationship to care recipients, healthcare access, socioemotional support, dementia patient diagnosis, engagement in intervention, relationship quality with facilitator, hours (weekly) spent with the person with dementia. Any variables showing significant group differences will then be considered confounds and included in the main statistical analyses. We will also check for missing data and signs of systematic response bias in self-reported responses. The main analysis will evaluate the effect of treatment group x time (t0, t1, t2). All participant outcome measures (domains: relational well-being, psychological well-being, dementia patient’s lifestyle changes), will be analyzed using generalized linear mixed models. Models will treat treatment and time points (including their interaction) as fixed effects and caregivers as random effects. We will look for a main treatment effect, a main time effect, and an interaction effect of treatment by time. All hypotheses will be individually evaluated at a nominal *p*-value of 0.05.

Semi-structured interviews will be analyzed using thematic analysis. First, grounded theory’s open coding stage will be employed, followed by axial coding and analyses (Spradley, 1979; Charmaz, 2006). We will identify meaningful themes and conceptualize our findings in relation to existing mindfulness theories and stress reactivity research. Because the first two authors are mindfulness teachers who have worked extensively with older adults, including dementia caregivers, qualitative data will be analyzed separately and jointly by the first two authors. Final synthesis of analyzed data will be obtained through continuous discussions among the research team until consensus is reached.

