### Strategies for improving adherence

Throughout the study, participation in both arms will be monitored, and retention enhanced *via* emails and calls. In the mindfulness-based intervention participants attending at least five of eight sessions will be defined as completers and will be included in the final analysis, though the number of completed sessions will be evaluated as a potential confound. To document participants’ daily mindfulness practice throughout the course, a weekly online survey will be employed accounting for home practice frequency and quality. In the active control arm, participants’ progress and skill completion can be monitored online by study staff; participants completing 75% of the material before the T1 assessment and attending at least one in-person session will be included in the final analysis, though different levels of completion will be evaluated as a potential confound.

Interventions may be discontinued at the participant’s request, with case-by-case evaluation of causative factors (e.g., death of care-recipient, acute trauma, intense amount of stress/grief, scheduling conflict). Any participant not meeting the preset participation thresholds will not be excluded from completing the remainder of the study, but their data will not be analyzed. Some attrition is expected, but with enhanced retention *via* direct contact with participants, we believe we can retain 80% of participants through the entire intervention and T1 assessment.

While we suggest a fairly broad array of assessment measures in this protocol, the overall time to complete them is ~1 h. In our two decades of experience performing observational research with caregivers of dementia patients, we have found that 1 h of questionnaires is not typically experienced as unduly burdensome for these individuals. However, individuals with more extreme current stressors could find the time demand for participation in the protocol daunting, thus they are fully informed of the demands on their effort during the informed consent process, at which time they will have the option to decline to participate.

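### The stated power (80% at r = 0.70, 25% at r = 0.50) cannot be obtained from 20 per arm at alpha 0.05, whether r is a correlation or a standardised mean difference

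*Protocol article*

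**What the plan says.** The Sample size calculation section says that no effect sizes have been published for this intervention and that more than 20 per arm was impractical. It concludes that "this sample size will only be powered to detect large between-group effect sizes", and quantifies this as "80% power to detect *r* > =0.70; 25% power to detect *r* > = 0.50". It does not say what r is, which test was assumed, whether that test was one- or two-sided, or how many participants were taken as analysed after attrition.

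The other inputs appear elsewhere in the article:

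- Enrolment (Recruitment, consent, and allocation to interventions): "Recruitment is planned to continue until 40 eligible participants are enrolled (20 per intervention arm").
- Allocation (text after Table 1): "Randomization with 1:1 allocation ratio to one of the two arms".
- Retention (Strategies for improving adherence): "we believe we can retain 80% of participants through the entire intervention and T1 assessment".
- Significance level (Data analysis plan): "All hypotheses will be individually evaluated at a nominal *p*-value of 0.05".

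**The concern.** For 32 to 40 people split into two equal groups, a correlation of 0.70 is a very large effect, and power for it should be close to certain, not 80%. If r was written where a standardised difference d was meant, 0.70 is too small for 80% power with groups of this size. The label therefore fails on both readings, and in opposite directions.

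The fall from 80% to 25% between 0.70 and 0.50 is also too steep for a 0.05 test.

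This is the article's only numerical power statement. A reader facing a null result needs to know whether an effect of 0.50 was nearly undetectable or quite likely to be found, and the sentence does not tell them. The Discussion also suggests that further rounds could bring the sample to acceptable power, a judgement that needs a correct starting figure.

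**Working it through.** **Inputs from the article.** 20 enrolled per arm, 1:1 allocation; 80% retained, so 0.80 × 20 = 16 per arm (32 in total); alpha 0.05 per hypothesis. Sidedness is not stated, so I take two-sided and check one-sided below.

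**1. Effects read as standardised mean differences d.** Two-sample t-test: noncentrality = d × √(n/2), df = 2n − 2, power from the noncentral t.

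- n = 16: √(16/2) = 2.828, so the noncentrality is 1.980 at d = 0.70 and 1.414 at d = 0.50. With a critical t of 2.042 on 30 df, power is **48.3%** and **27.8%**.
- n = 20: noncentrality 2.214 and 1.581, critical t 2.024 on 38 df, power **57.8%** and **33.8%**.

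**2. Effects read as correlations.** Fisher z: power = Φ(atanh(r) × √(N − 3) − 1.96), with atanh(0.70) = 0.867 and atanh(0.50) = 0.549.

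- N = 32: 0.867 × √29 − 1.96 = 2.71, power **99.7%**; 0.549 × √29 − 1.96 = 1.00, power **84.1%**.
- N = 40: above **99.9%** and **91.6%**.
- Converting instead by d = 2r/√(1 − r²) gives d = 1.96 and 1.155. At 16 per arm the t-test then has more than 99.9% and 88.5% power.

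**3. Do the two figures agree with each other at alpha 0.05?** This check does not depend on n (normal approximation). 80% power requires a standardised effect of 1.960 + 0.842 = 2.802.

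- On the d scale, moving from 0.70 to 0.50 scales this to 2.802 × 0.50/0.70 = 2.001, so power is Φ(2.001 − 1.960) = about **52%**.
- On the Fisher scale it becomes 2.802 × 0.549/0.867 = 1.775, so power is Φ(−0.185) = about **43%**.
- With the r-to-d conversion the figure is about **38%**.

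None is 25%. Equivalently, the sample sizes needed differ:

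| Reading | 80% at 0.70 | 25% at 0.50 |
|---|---|---|
| d, per arm | about 33 | about 14 |
| correlation, total N | 13–14 | 8–9 |

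An unstated attrition rate therefore cannot reconcile the pair.

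**4. Other readings tried at alpha 0.05.** Power at 0.70 and at 0.50:

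| Variant | 16 per arm | 20 per arm |
|---|---|---|
| d, one-sided | 61.4% / 39.6% | 70.2% / 46.3% |
| Cohen's f | 96.9% / 78.1% | 99.1% / 86.9% |
| Correlation, per-arm n used as N | 87.8% / 50.8% | 94.7% / 62.0% |
| d, baseline-adjusted, assumed T0–T1 correlation 0.5 | 60.0% / 35.2% | 70.2% / 42.9% |
| d, baseline-adjusted, assumed T0–T1 correlation 0.7 | 76.5% / 48.3% | 85.6% / 57.8% |

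No row gives 80% and 25% together. The pair can be matched only at much stricter levels. With Fisher z, for example, N = 26 at alpha 0.001 gives 80.8% and 25.6%. That is not the stated 0.05.

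**5. What the design can detect with 80% power (t-test, two-sided 0.05).** d = 1.02 at 16 per arm, which is r = 1.024/√(1.024² + 4) = 0.46; d = 0.91 (r = 0.41) at 20 per arm. With baseline adjustment at 16 per arm, multiply by √(1 − ρ²): 1.024 × 0.866 = 0.89 for an assumed ρ of 0.5, and 1.024 × 0.714 = 0.73 for 0.7.

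**The case against.** The strongest reply is that the figure decides nothing. The article calls the study an exploratory pilot, sets 20 per arm by practicality, and warns in the Discussion that it may be underpowered. Its verbal conclusion, that only large effects are detectable, survives: d = 1.02 is large. All of this is correct, and it limits the consequence to interpretation. It does not make the printed numbers right.

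Second, the direction of the error is unknown. Read literally as a correlation, the statement understates power, which is cautious; the overstatement arises only if d was meant. That also stands, and it is a reason to define the metric, since the pair is wrong on both readings.

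Third, the planned analysis is a mixed model over three visits, so an unadjusted t-test at one visit is not its exact power. This is fair. An assumed baseline correlation of about 0.7 would bring d = 0.70 near 80%, but it lifts d = 0.50 to 48–58%, so the 25% then fails. The article gives no within-person correlation from which to state model-based power.

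Finally, the 25% taken alone is close to the d reading (27.8% at 16 per arm, 24.7% at 14). On that reading the clear failure is the 80%.

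**Conclusion.** The power statement is wrong as written. At 16 per arm and two-sided 0.05, power at 0.70 is 48% on the d scale, 32 percentage points below the claim. On the correlation scale, power at 0.50 is 84%, 59 points above the claim. No single sample size at alpha 0.05 gives both figures on either scale.

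The recomputed values assume a two-sided, unadjusted comparison of two equal groups and the article's 80% retention. The one-sided, full-retention and baseline-adjusted variants change the values but not the conclusion. The choice of N = 40 is unaffected.

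**What to change.** Name the effect-size metric, analysed number, test and sidedness, and replace the parenthesis with a sentence such as:

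*With 16 retained per arm and a two-sided alpha of 0.05, a two-sample comparison has 80% power for a standardised mean difference of 1.02 (r about 0.46), 48% for 0.70 and 28% for 0.50, before baseline adjustment.*

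If the sponsor wants to credit the mixed model, the assumed within-person correlation should be stated with the result, for example 80% power at d = 0.89 to 0.73 for correlations of 0.5 to 0.7.

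The cost is one sentence. N stays at 40, and no analysis or outcome changes. If d was meant, the stated sensitivity becomes less favourable; if a correlation was meant, it becomes more favourable.
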